## Abstract

**Background:**

The coronavirus disease 2019 (COVID-19) is caused by the severe acute respiratory syndrome coronavirus 2 (SARS-CoV-2) that was first identified in Wuhan, Hubei, China, in December 2019. It was recognized as a pandemic by the World Health Organization on 11 March 2020. Outbreak forecasting and mathematical modelling suggest that these numbers will continue to rise. Early identification of effective remedies that can shorten the duration and severity of illness is critical for Lagos State, which is the epi-centre of the disease in Nigeria.

**Methods:**

This is a multi-centre, randomized, double-blind placebo-controlled superiority trial. The study investigates the efficacy of chloroquine phosphate, hydroxychloroquine sulphate and lopinavir/ritonavir added on to standard of care compared to standard of care only in patients with COVID-19 disease. The primary outcome is the clinical status of patients measured using a 7-point ordinal scale at day 15. Research participants and clinicians will be blinded to the allocated intervention. Outcome measures will be directly assessed by clinicians. Statistical analysis will be done by a team blinded to the identity and allocation of research participants. Data analysis will follow intention-to-treat methods, using R software.

**Discussion:**

The current study is of strategic importance for Lagos State in potentially curbing the health, social and economic burden of COVID-19 disease. Should the current study demonstrate that either of the three intervention drugs is more efficacious than standard therapy alone, the State Ministry of Health will develop an evidence-based guideline for the management of COVID-19 in Lagos State. The findings will also be shared nationally and with other states which may lead to a standardized national guideline for the treatment of COVID-19 in Nigeria.

**Trial registration:**

Pan African Clinical Trials Register PACTR202004801273802. Registered prospectively on April 2, 2020

**Supplementary Information:**

The online version contains supplementary material available at 10.1186/s13063-021-05675-x.

## Introduction

### Background and rationale {6a}

#### Study rationale

The severe acute respiratory syndrome coronavirus 2 (SARS-CoV-2) causes the coronavirus disease 2019 (COVID-19), and it was first detected in Wuhan, China, in December 2019 [1]. COVID-19 disease was recognized as a pandemic by the World Health Organization (WHO) less than 3 months after on the 11th of March 2020 [2]. By July 1, 2020, more than 10,357,662 cases of COVID-19 had been reported, with about 508,055 deaths globally [3, 4]. COVID-19 outbreak forecasts and mathematical models suggest that the size of the population affected will continue to rise [5] in the coming months.

The virus is typically spread from one person to another via respiratory droplets produced during speech, coughing and sneezing [6]. Primarily, it spreads when people are in close contact, but it may also spread when one touches a contaminated surface and then their eyes, nose or mouth. It is most contagious when people are symptomatic, although spread may be possible before symptoms appear. The time between exposure and symptom onset is typically around 5 days but may range from 2 to 14 days. Fever and chills and dry cough, as well as shortness of breath, are commonly reported symptoms [1]. Complications may include pneumonia and acute respiratory distress syndrome. A WHO investigative report indicates that age over 60 years, diabetes mellitus, cardiovascular disease, chronic respiratory disease and cancer are associated with the highest risk of severe disease and death [1].

In Nigeria, a total of 26,484 cases and 603 deaths had been reported as of 1 July 2020 with Lagos alone accounting for about half of the cases [7]. The high proportion of cases contributed by Lagos State is likely due to the fact that it is the commercial capital with a large number of international travellers and has COVID-19 testing facilities and a very large population compared to other states.

Coronavirus is a type of single-stranded positive-strand RNA virus with an envelope [8]. Currently, there is no specific therapy for coronavirus infections. Only a limited number of treatment studies have been conducted because most human coronavirus strains cause self-limiting disease and care is supportive. However, after the severe acute respiratory syndrome (SARS) coronavirus was identified in 2002 and caused a large global outbreak, there was an increased interest in the development of specific therapeutic agents. SARS-CoV case-patients were treated with corticosteroids, chloroquine phosphate, hydroxychloroquine, convalescent plasma, and lopinavir or ritonavir, and, except for ribavirin, many of these agents have in vitro preclinical data that support their efficacy [9–19]. Since the SARS outbreak, new therapeutic agents targeting viral entry proteins, proteases, polymerases and methyltransferases have been tested; however, none of them has been shown to be efficacious in clinical trials [20–22].

There are reports about the potential value of a number of drugs [9–12, 23]. Of the various therapeutic interventions that have been suggested as being potentially effective, chloroquine stands out as an attractive option for the treatment of COVID-19 in Nigeria, if found to be efficacious. It has been used extensively for the treatment of malaria in Nigeria and is low-cost. Clinically, it has been reported that chloroquine improves outcomes in patients with COVID-19 [24–26]. However, robust clinical trials are still required to prove their effectiveness and safety in the treatment of COVID-19 due to limitations in the design of reported clinical studies. Furthermore, there are recent reports of chloroquine poisoning following announcements of its potential effectiveness in the treatment of COVID-19 [27]. This compelled a notice by the Nigeria Centre for Disease Control (NCDC) publicly stating that chloroquine is not an approved treatment for COVID-19 [28].

Chloroquine has been used clinically since 1944, primarily for the prevention and treatment of malaria [29]. More recently, it has been shown to have antiviral activity against HIV-1, avian influenza H5N1, HCoV-229E, hepatitis B and herpes simplex type 1 viruses [29–32]. Chloroquine’s anti-SARS-CoV activity involves a variety of mechanisms that inhibit virus replication such as suppressing phosphatidylinositol binding clathrin assembly protein (PICALM), inhibiting endosomal acidification required for virus/cell fusion and reducing terminal glycosylation of angiotensin-converting enzyme 2 (ACE2) receptors [31, 33, 34]. Chloroquine also suppresses tumour necrosis factor alpha and interleukin 6, which mediate the inflammatory complications of viral infection [29].

The inhibition of infection at the cellular level has been shown to occur at a 50% inhibitory concentration (*IC50*) of 8.8 ± 1.2 μM for SARS-CoV [31] and 50% maximal effective concentration (*EC50*) of 1.13 μM for SARS-CoV-2 [9]. Furthermore, an *EC90* of 6.9 μM was achieved for SAR-CoV-2 [9]. These findings are significant because they suggest that therapeutic doses needed for effective anti-SARS-CoV-2 activity are similar to doses used in the treatment of malaria, which is endemic in Nigeria, and rheumatoid arthritis [31, 35]. Hydroxychloroquine has not been studied to the same extent, but it appears to have more potent in vitro efficacy [36]. These concentrations of chloroquine are significantly lower than the 50% cytotoxic concentration (*CC50*) which ranged from greater than 100 μm to 261.3 ± 14.5 μm with selectivity index from 30 to more than 88 [9, 31].

Despite the promising results from in vitro studies, chloroquine has not been shown conclusively to be efficacious in the treatment of COVID-19. However, it is now part of the recommendations for treatment in several countries while awaiting results of planned and on-going clinical trials [23, 36]. These recommendations have been informed by two main sources—an expert consensus on chloroquine phosphate for treatment of COVID-19 from China and a clinical study undertaken in France [26, 37]. These and one other small study reported from China suggest that chloroquine and hydroxychloroquine prevent the worsening of pneumonia, facilitate the clearance of the virus and shorten the duration of COVID-19 [24–26, 37].

There are very few clinical studies on the efficacy of chloroquine phosphate or hydroxychloroquine sulphate. In the main study that has generated expectations of a cure, hydroxychloroquine appeared to lead to a rapid decline in nasopharyngeal viral load with negative viral cultures in almost all patients at day 5 [26]. The duration of hospital admission was also short averaging 5 days. Although impressive, this evidence is considered weak [23], due to the methodological design of the study which had a small sample size and no control group.

Similar to chloroquine phosphate and hydroxychloroquine sulphate, there are few clinical studies investigating the effect of lopinavir/ritonavir in the treatment of COVID-19 disease [38]. The combination of antiviral serum protease inhibitors lopinavir and ritonavir has been touted as a potential therapy for COVID-19 disease. Both drugs have historically been used to manage human immunodeficiency disease type 1 (HIV-1) and found to have an in vitro inhibitory effect on the SARS-CoV virus [11, 23, 39, 40]. The antivirals work synchronously with ritonavir which inhibits the enzyme cytochrome P450 and by effect increases the plasma half-life of lopinavir [11].

Cao et al. [38] conducted an open-label randomized controlled trial in hospitalized patients using lopinavir/ritonavir in combination with standard care therapy. The study found that lopinavir/ritonavir in combination with standard therapy did not provide a clinical benefit or reduce mortality compared to standard therapy alone. However, the study was not blinded, meaning the knowledge of the assigned treatment could have biased the findings of the outcome assessors.

The relatively high morbidity associated with COVID-19 and potentially inappropriate use of publicized remedies means that identifying effective medications that can reduce the duration and severity of illness is a high priority globally. The World Health Organization is taking steps towards a multi-country clinical trial of potential therapeutic agents [41]. This study is being undertaken as part of global efforts to identify effective specific therapeutic agents for COVID-19.

Broadly, this study, is asking three different questions, namely (i) does chloroquine phosphate safely improve patient outcome when added to the standard treatment for COVID-19 compared to the addition of placebo?; (ii) does hydroxychloroquine sulphate safely improve patient outcome when added to the standard treatment for COVID-19 compared to the addition of placebo?; and (iii) does lopinavir/ritonavir safely improve patient outcome when added to the standard treatment for COVID-19 compared to the addition of placebo?

#### Importance of the Lagos COVID-19 Treatment Trial

Early identification of effective remedies that can shorten the duration and severity of illness is critical for Lagos State and Nigeria. The COVID-19 pandemic places an enormous burden on the Nigerian health system which already faces significant resource constraints. There is a limited number of hospital beds, especially, for infectious diseases requiring isolation and severely ill patients who need high dependency or intensive care. The availability of such treatment would reduce morbidity and mortality and increase the availability of hospital beds, thereby, enabling management of the epidemic without compromising care for patients with other diseases. Effective treatment may also lead to an earlier resolution of the pandemic.

Testing these drugs in a robust trial is important because it would help determine conclusively whether or not they are efficacious. If they are, then the scenario above applies, while if they are not then efforts can be redirected to examine other potential remedies and resources would not be spent on ineffective therapies.

## Objectives {7}

To evaluate the clinical efficacy of chloroquine phosphate, hydroxychloroquine sulphate and lopinavir/ritonavir added on to standard therapy relative to standard therapy alone for treatment of individuals with laboratory-confirmed COVID-19
1.1.To evaluate the clinical efficacy of chloroquine phosphate added on to standard therapy relative to standard therapy alone for treatment of individuals with laboratory-confirmed COVID-191.2.To evaluate the clinical efficacy of hydroxychloroquine sulphate added on to standard therapy relative to standard therapy alone for treatment of individuals with laboratory-confirmed COVID-191.3.To evaluate the clinical efficacy of lopinavir/ritonavir added on to standard therapy relative to standard therapy alone for treatment of individuals with laboratory-confirmed COVID-19

The secondary objectives are:
To evaluate the effect of chloroquine phosphate, hydroxychloroquine sulphate and lopinavir/ritonavir added on to standard therapy compared to standard therapy on the rate of progression/resolution of COVID-19
1.1.To evaluate the effect of chloroquine phosphate added on to standard therapy compared to standard therapy on the rate of progression/resolution of COVID-191.2.To evaluate the effect of hydroxychloroquine sulphate added on to standard therapy compared to standard therapy on the rate of progression/resolution of COVID-191.3.To evaluate the effect of lopinavir/ritonavir added on to standard therapy compared to standard therapy on the rate of progression/resolution of COVID-192. To evaluate the safety of chloroquine phosphate, hydroxychloroquine sulphate and lopinavir/ritonavir added on to standard therapy compared to standard therapy in the treatment of individuals with laboratory-confirmed COVID-19
2.1.To evaluate the safety of chloroquine phosphate added on to standard therapy compared to standard therapy in the treatment of individuals with laboratory-confirmed COVID-192.2.To evaluate the safety of hydroxychloroquine sulphate added on to standard therapy compared to standard therapy in the treatment of individuals with laboratory-confirmed COVID-192.3.To evaluate the safety of lopinavir/ritonavir added on to standard therapy compared to standard therapy in the treatment of individuals with laboratory-confirmed COVID-19

## Trial design {8}

This is a multi-centre, randomized, double-blind, placebo-controlled multi-arm clinical trial with a parallel group and superiority design. There are three treatment arms and one control arm with equal distribution of participants between the arms. If the intervention drug for any arm is not available, then participants will be allocated equally to each of the available arms.

## Methods: participants, interventions and outcomes

### Study setting {9}

This trial will take place at health facilities designated for COVID-19 patients in Lagos State, Nigeria. The LACTT trial will be conducted at three of the health facilities designated for COVID-19 patients in Lagos State, Nigeria. The centres are Lagos Mainland Infectious Disease Hospital, Yaba; the Eti-Osa COVID-19 Isolation and Treatment Centre; and the Onikan COVID-19 Isolation and Treatment Centre Lagos State. The three centres manage patients domiciled in Lagos State, based on a similar state-wide protocol which aligns with the Nigeria Centre for Disease Control guideline for testing and management of COVID-19 disease. The proposed sample size distribution across the three centres is 200 participants per centre.

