## Outcomes {12}

COVID-19 is a new disease and our understanding of it is evolving. To align this study with other international studies, the objectives, endpoints and some other aspects of the WHO’s Master Protocol [42] have been adopted as appropriate with modifications to suite the Lagos context. There are three objectives—one primary and two secondary objectives. Each objective has three sub-objectives—one for comparing chloroquine phosphate added on to standard therapy and standard therapy alone; one for comparing hydroxychloroquine sulphate added on to standard therapy and standard therapy alone; and one for comparing lopinavir/ritonavir added on to standard therapy and standard therapy alone.

A special WHO committee developed the ordinal scale that will be used in this study for the primary endpoint [43]. This study uses a combined endpoint (based on the WHO 7-point ordinal scale) of both “clinical status and mortality” at day 15. Hence, superiority can be demonstrated when either arm shows a significant effect on the variables for clinical status OR mortality by day 15. This endpoint is particularly useful in our population given the low mortality rate, and a combined endpoint would increase the study power. The secondary endpoints will enable evaluation of the effect of the trial medications on the rate of change in the clinical condition of COVID-19 patients, as well as the safety of the trial medications (Table 3).

**Table 3 Tab3:** LACTT objectives and endpoints

**Primary objectives**	**Primary endpoints**

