## Sample size {14}

The sample size of 200 per arm has been calculated assuming an odds ratio (*OR*) of 2, 85% power and a 2-tailed test at level *α* = 0.05 and allowing for approximately 10% of participants to be lost to follow-up. The odds ratio represents the odds of improvement in the ordinal scale for treatment relative to control.

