## Assignment of interventions: allocation

### Sequence generation {16a}

Prior to study initiation, a randomization list will be generated (using the statistical programming language R, version 3.6.3 to enable random assignment to each of the trial arms at each of the study sites using an equal allocation ratio (for instance 1:1:1:1 for four arms)). If arms are added to or dropped from the trial, randomization will proceed with an equal probability of assignment to each of the remaining arms.

Randomization will be stratified by site and at each site by severity of illness at enrollment yielding two strata: (1) asymptomatic (no clinical symptoms or signs) and (2) symptomatic (presence of clinical symptoms and/ or signs). The R code used to generate the randomization lists will store the seed so that the generated lists are reproducible.

The randomization list will be generated using permuted block randomization with two block sizes, with the larger block size chosen so that it is not a multiple of the smaller block. Using permuted block randomization rather than simple randomization will avoid the possibility of long periods of time during which participants are not allocated to one or more arms of the study—a scenario which could introduce bias to the study due to time effects. Two block sizes would make it more difficult for clinicians (who will be unaware of the block sizes) to guess any part of the allocation sequence, thus, reducing the potential for the introduction of selection bias by well-meaning staff members at study sites.

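### Four equal arms of 200 need 800 participants, but three centres of 200 supply 600; no overall total says which governs

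*Protocol article*

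**What the plan says.** Three parts of the protocol article bear on the total.

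- Sample size {14}: "The sample size of 200 per arm has been calculated assuming an odds ratio" of 2, with "85% power and a 2-tailed test at level" 0.05, and "allowing for approximately 10% of participants to be lost to follow-up". The effect is defined thus: "The odds ratio represents the odds of improvement in the ordinal scale for treatment relative to control".
- Trial design {8}: "There are three treatment arms and one control arm with equal distribution of participants between the arms". Sequence generation {16a} agrees: "using an equal allocation ratio (for instance 1:1:1:1 for four arms".
- Study setting {9} names three centres and adds: "The proposed sample size distribution across the three centres is 200 participants per centre".

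The article gives no overall number of participants. Under Interim analyses {21b}, safety looks are placed at about 25%, 50% and 75% of total enrolment and efficacy looks at the same fractions of total information. Stopping is to be considered if conditional power under the original assumptions is below 20%.

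**The concern.** The per-arm and per-centre figures imply different trial sizes. Both are in current text, so a separate analysis plan could not make them agree.

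The power claim is attached to 200 per arm. If sites are set up and closed on the basis of 200 each, the four-arm trial ends with three quarters of the participants that the claim assumes. Each of the three comparisons with control would then be more likely to miss a true odds ratio of 2. That matters for a trial whose rationale says it should settle conclusively whether these drugs work.

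The total is also needed to place the interim looks and to define the planned end of the trial when conditional power is computed.

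**Working it through.** **Inputs, all from the protocol article.** Four arms, equal allocation (Trial design {8}; Sequence generation {16a}). 200 per arm, odds ratio 2, 85% power, two-sided α = 0.05, about 10% loss (Sample size {14}). Three centres, 200 each (Study setting {9}). Normal quantiles: 1.960 for two-sided 0.05 and 1.036 for 85% power; their sum is 2.996.

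**1. Totals.**
- By arm: 4 × 200 = 800.
- By centre: 3 × 200 = 600.
- Shortfall: 800 − 600 = 200, and 200/800 = 25%.

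**2. The plan's own figure.** With 10% loss, 200 per arm leaves 180 evaluable, or 360 for one comparison. The proportional-odds sample-size formula is

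N = 12(z_α + z_β)² / [(ln OR)² (1 − Σp̄³)],

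where p̄ are the category proportions averaged over the two arms. The part free of p̄ is 12 × 2.996² / (ln 2)² ≈ 224.2. For N = 360 this requires 1 − Σp̄³ = 224.2/360 = 0.623, which is attainable.

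The article gives no category distribution, so 200 cannot be reproduced uniquely. Under a range of assumed distributions the formula gives 128 to 317 per arm after inflation for loss. A two-category version with 25% or 60% of controls improving (both assumed) gives 174 evaluable, and 174/0.9 rounds up to 194. The stated 200 is therefore plausible and is taken as given below.

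**3. Consequence if 600 governs with four arms.**
- Per arm: 600/4 = 150. Evaluable: 150 × 0.9 = 135.
- With the odds ratio and outcome distribution fixed, the expected test statistic scales with the square root of sample size, so the unknown distribution cancels: power = Φ(2.996 × √(135/180) − 1.960) = Φ(2.595 − 1.960) = Φ(0.635) = 73.7%.
- With no losses at all: Φ(2.996 × √(150/180) − 1.960) = Φ(0.775) = 78.1%.
- Odds ratio detectable with 85% power at 135 evaluable: exp(ln 2 × √(180/135)) = exp(0.800) = 2.23.

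**4. Sensitivity to the efficacy looks.** If the final critical value is about 2.01 to 2.02 (an assumption for O'Brien-Fleming-type spending over four analyses), power is 73.5% if the stated 85% already allowed for the looks, and about 72% if it did not.

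**5. Interim counts.** The 25%, 50% and 75% points of enrolment fall at 150, 300 and 450 participants out of 600, or at 200, 400 and 600 out of 800.

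**The case against.** The sample-size section holds the only derivation in the article, and it says 200 per arm. The centre split sits in a setting paragraph and is only proposed, so it may simply be a slip. In that case the trial is planned at 800 and nothing is lost but a line of text. This stands. A reader might infer that the trial has 74% power, but the documents support that only conditionally.

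A second explanation is that 600 equals three arms of 200. The article provides for an arm being unavailable or dropped, and 600 would then keep the stated 85%. The arithmetic is right, but the article describes four arms throughout and nowhere links the 600 to a three-arm trial. If that is what was meant, it has to be written.

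A reader might also go further and argue that 200 per arm is itself too few. Asymptomatic and mild cases are eligible, and the Outcomes {12} section says "This endpoint is particularly useful in our population given the low mortality rate, and a combined endpoint would increase the study power", so day-15 scores could cluster in one category. The documents do not establish this. Moderate and severe cases are eligible too, no expected mix is given, and the assumed distribution behind an ordinal sample size is a detail often kept in another document. Step 2 of the working shows 200 to be attainable, so no error in it is claimed.

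Finally, the effect on monitoring is limited. The looks are defined as fractions, so the printed z-boundaries are the same at 600 and 800. Only the participant count at each look and the conditional-power input change.

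**Conclusion.** The contradiction holds and needs no assumption: the article's own figures give 800 by arm and 600 by centre, a gap of 200 participants or 25%, with no stated total to settle it.

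The loss of power is conditional. It applies if 600 is the intended total, all four arms run, loss is 10%, and the stated 85% at 200 per arm is correct. Power at an odds ratio of 2 is then about 74%, so the chance of missing that effect rises from 15% to about 26% in each comparison. With no losses power is about 78%, still short of 85%. If 800 is intended, the stated power is unaffected. The documents do not show which total was meant. A main design quantity should not be left in that state, so this must be corrected.

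**What to change.** State one overall total and carry it through Study setting {9} and Sample size {14}. There are two ways to do it.

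- **800 governs.** Replace the centre split with one that sums to 800 (800/3, about 267 per centre) and keep 200 per arm and 85%. As text this is one correction. In practice the centres must enrol 200 more in total than the setting section proposes, so the recruitment timetable should be checked against it.
- **600 governs.** Keep 200 per centre, restate 150 per arm (about 135 evaluable), and give power of about 74% at an odds ratio of 2, or 85% at an odds ratio of about 2.23. No extra participants are needed; the cost is a less favourable power statement.

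If 600 was meant for a three-arm trial, say so explicitly. In every case, use the chosen total to time the 25%, 50% and 75% looks and to compute conditional power. The z-boundaries can stay as they are.
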